**In case of any of the following circumstances, the clinical trial shall be terminated:**

- Sponsor has found that the vaccine has potential safety hazards or the trial has quality related problems, and requiring the complete termination of the study.
- The Ethics Committee requests the termination of the trial because of the violation of ethics in the trial.
- The administrative authority requests the termination of the trial

CONFIDENTIAL

---

## 7.8 Protocol Violation and Deviation

### 7.8.1 Protocol Violations

The list of protocol violations is as follows (including but not limited to):

- Fail to obtain participant's informed consent;
- Participants who did not meet the inclusion criteria or met the exclusion criteria were enrolled in the study;
- Participants received wrong research interventions (such as incorrect vaccinations);
- Fail to report serious adverse events (SAE) within specified time;
- Received other investigational vaccines during the study period.

### 7.8.2 Protocol Deviations

The list of protocol deviations is as follows (including but not limited to):

- Not receive the investigational vaccine within the window period;
- Not collect blood within the window period;
- The interval between vaccination and other vaccines is not long enough, except for emergency vaccination such as rabies.

## 7.9 Study Duration

Early Participant Recruitment: 1 month;

Booster Vaccination + immune persistence observation: about 13 months

Sample Testing: approximately 1 month

Complete the Summary Report: about 1 month

## 7.10 Site Close

All participants completed long-term safety observation for 12 months after vaccination and blood collection for 12 months after immunization. Trial sites will be closed and immune persistence evaluation will be initiated only once the following activities have been completed:

1. Completed all study requirements according to the study protocol
2. Locked the database
3. Clarification of data by the statistician (blind audit)
4. Unblinded the necessary study staff to evaluate the safety, immunogenicity and

**CONFIDENTIAL**

---

vaccine efficacy.

## **8. SAFETY DEFINITION, REPORTING AND MONITORING**

### **8.1 General Precautions**

Before the start of the trial, the Sponsor shall strictly examine the trial site in accordance with GCP requirements, focusing on whether the environmental facilities of the trial site meet the requirements of "Vaccination Management Standards" and "Guiding Principles for Quality Management of Vaccine Clinical Trials". Ensure the first aid facilities and first aid equipment in the first aid room are complete and effective, and the first aid doctors have corresponding qualifications and capabilities. Emergency related personnel (emergency doctors, emergency nurses, ambulance drivers, etc.) are trained to be qualified and familiar with the transfer routes and procedures of the agreed hospital. They are on standby at the trial site during vaccination. The trial site shall be equipped with ambulances. The ambulance shall be parked in a fixed position to keep the vehicle in good condition and in an emergency and shall be under the command and transfer of the emergency response team at any time. During the vaccination period, the agreement hospital will make daily preparations for medical personnel, instruments and equipment, first aid drugs and first aid sites to ensure that the participants can receive timely treatment. The trial site shall formulate an emergency plan, stipulate personnel responsibilities, contact numbers, rescue routes and other measures to ensure timely handling of unexpected adverse events, and ensure effective contact between participants and investigators so that any adverse events can be reported and handled quickly.

### **8.2 Risk Prevention Measures Related to COVID-19**

#### **(1) Trial site consideration**

Investigators during recruitment should confirm whether there are COVID-19 infections or suspected cases in the same community by investigating or inquiring volunteers. Whether fever, dry cough, fatigue, nasal obstruction, runny nose, sore throat, myalgia, diarrhea, shortness of breath and dyspnea occurred recently.

#### **(2) Strengthen the management and personal protection of participants during the study period**

**CONFIDENTIAL**

Disinfection of each functional area of clinical research should be strictly done in the test site according to regulations, and windows should be opened and ventilated regularly. Strictly implement independent areas and special passages, and the recipients and their accompanying personnel wait in relative divisions to avoid contact with people other than research doctors and nurses; All functional areas and public places should be equipped with hand disinfectants and temperature measuring devices, and recipients and their accompanying personnel entering the clinical research site should be equipped with masks to disinfect their hands and measure their body temperature.

The trial site shall strictly disinfect each functional area of clinical research according to regulations, and regularly open windows for air-ventilation. Strict implementation of independent areas and special passages, recipients and their accompanying personnel waiting in relative zones, to avoid contact with research doctors, nurses and other personnel other than research; All functional areas and public places should be equipped with hand disinfectants and temperature measuring devices. Recipients entering the clinical research site and their accompanying personnel are required to be equipped with masks to disinfect their hands and measure their body temperature.

During the first dose of inoculation, the on-site investigators shall remind the participants to strengthen their own protection. If COVID-19 pandemic occurs locally, the participants shall be provided with necessary protective materials such as masks, alcohol, etc. in time, and close attention to the health status of the participants shall be drawn, especially the symptoms related to COVID-19.

### **(3) Detection of COVID-19 RT-PCR**

Participants need to be tested for COVID-19 RT-PCR before first vaccination. Investigators need to regularly follow up and track the participants to identify whether they have developed fever, dry cough, fatigue and other symptoms recently. If the above symptoms exist, the participants will be collected samples for etiological detection of SARS-CoV-2 according to the prevention and protection policy for COVID-19 and based on the symptoms of the participants, or are advised to go to the hospital for blood testing and radiographic examination. If there are no symptoms such as fever, dry cough and fatigue, the participant

**CONFIDENTIAL**

should be home isolated according to the requirements of COVID-19 prevention and control protocol.

### **8.3 Handling and Reporting of Serious Adverse Events**

Serious adverse events refer to adverse medical events such as disability or loss of function, the need for hospitalization or prolonged hospitalization of participants, and congenital abnormalities or birth defects.

Monitoring and reporting of adverse events in vaccine clinical trials are jointly completed by participants, serious adverse event investigators, trial sites and responsible institutions at different observation time points with different stages.

The Sponsor is the main body responsible for monitoring, evaluating and SAE reporting safety information of vaccine clinical trials. Designated person acts as the administrator for clinical trial safety information monitoring and SAE reporting, and work with investigators to establish SOPs for clinical trial safety information monitoring and SAE reporting, know well the latest status of the safety information of the whole clinical trial, and timely report updates to all clinical trial institutions/ investigators and regulatory authorities.

If it is difficult to make a judgment on the correlation between SAE and vaccine or there is doubt about the judgment, when it is necessary to make a new judgment, the expert meeting shall make a judgment after argumentation.

#### **(1) On-site Treatment Measures**

Emergency plans for SAE treatment in clinical trials shall be established at the trial site, and all relevant personnel shall be trained. If the participants show serious adverse events, the investigators shall immediately take appropriate measures for the participants and record them. The investigators must take relevant approaches to know in time any clinically significant diseases/events related to vaccination. According to relevant national regulations, the participants should be received appropriate treatment in time in the designated hospitals.

Investigators at the trial site should follow up serious adverse events until the symptoms disappear or stabilize. The progress and outcome of all symptoms will be recorded in detail, and all drug treatments and medical treatments will be recorded at each follow-up.

**CONFIDENTIAL**

Investigators should truthfully record serious adverse events, which shall be evaluated and discussed in the final report after the test is completed or terminated.

During the whole observation process, if the participants suffer from physical injuries caused by serious adverse reactions related to vaccination, which is confirmed by the expert investigation team, the local insurance company will give corresponding compensation.

## **(2) Reporting Procedures for Serious Adverse Events**

### ***Reporting procedures of investigators include:***

Any serious adverse event, whether related to the investigational vaccine, the investigator must submit the initial report of the "Serious Adverse Event Report Form" to the drug administration department, the Sponsor and the ethics committee by fax, e-mail or EDC system or personal delivery within 24 hours after learning about it. Subsequently, the follow-up report of the "Serious Adverse Event Report Form" shall be submitted regularly until the end of the event. All information is reported in the "Serious Adverse Event Report Form" in the form of written reports, including description of adverse reactions/events, onset time and type, duration, intensity, causal relationship with vaccination, results, treatment methods (symptomatic treatment) and other relevant clinical and laboratory data. When receiving the report of serious adverse events/reactions, the investigator shall, together with the Sponsor, comprehensively consider the duration, scope, intensity, outcome and the willingness of the participant to decide whether the participant should continue to participate in the study or withdraw from the study in advance.

### ***Reporting procedure of Sponsors include:***

During the clinical trial of drugs, Sponsors need to quickly report unexpected and serious adverse reactions (SUSAR) that are definitely related to or suspicious of the tested drugs in the form of case-by-case safety reports according to the Standards and Procedures for Rapid Reporting of Safety Data during Clinical Trial of Drugs. If the researcher and the Sponsor cannot reach an agreement on the judgment of the causal relationship between adverse events and drugs, either party's judgment cannot exclude those related to the test drugs, and the Sponsor should also make a quick report.

**CONFIDENTIAL**

For SUSAR that is fatal or life-threatening, the Sponsor should report it as soon as possible after the first knowledge, but not more than 7 days, and report it within the following 8 days to improve the follow-up information (Note: the day when the Sponsor first learned it is the 0th day). For SUSAR that is not fatal or life-threatening, the Sponsor should report it as soon as possible after the first knowledge, but not more than 15 days. For other potential serious safety risk information, the Sponsor should also report to the national drug evaluation agency as soon as possible, and at the same time make medical and scientific judgment on each situation. After the first report, the Sponsor shall continue to track the serious adverse reactions and submit relevant new information or changes to the previous report in a timely manner in the form of a follow-up report. The reporting time limit shall be within 15 days from the date of obtaining the new information.

#### **8.4. Outcome of Serious Adverse Events**

The outcomes of serious adverse events include:

1. Symptoms resolved (with sequelae);
2. Symptoms resolved (without sequelae);
3. Symptoms persist;
4. Require hospitalization;
5. Require medical intervention to prevent serious outcomes; and
6. Death.

### **9. COMPLETION OF CLINICAL TRIAL**

After obtaining the immunogenicity test results 14 days after the full course of immunization, completing the safety follow-up for 28 days, ensuring the authenticity, integrity and accuracy of clinical trial data, the database is locked and unblinded to perform safety, immunogenicity and vaccine efficacy evaluation, and blood collections for 12 months immune persistence are completed, the study site will be closed.

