### 4.3. Study Endpoint

**CONFIDENTIAL**

**Primary Endpoints:**

1. GMT and the 4-fold rise rate of anti-omicron neutralizing antibody 14 days after a single dose of the booster vaccine in adults  $\geq 18$  years of age.
2. The incidence and severity of any adverse reactions/events within 30 minutes after vaccination;
3. The incidence and severity of solicited adverse reactions/events within 0-7 days after vaccination;
4. The incidence and severity of unsolicited adverse reactions/events within 8-30 days after vaccination;
5. The incidence of SAE and AESI observed after vaccination and up to 12 months after full course of immunization.

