## 6.2 Vaccine Packaging and Labeling

All investigational vaccines are packaged in doses in boxes with the same appearance and only marked by the vaccine number. Each study ID will be matched with a unique vaccine number, the format of the vaccine number is AE+4-digit Arabic number. See the following label for detailed information.

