**CONFIDENTIAL**

**Recombinant COVID-19 Vaccine (NVSI-06-09)****(For Clinical Research Use Only)**

Vaccine Number: AExxxx

Batch Number: XXXX

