**CONFIDENTIAL**

### 6.3.3 Vaccine Records

***Vaccine handover records:*** The Sponsor will provide investigational vaccines, control vaccines (placebo) and vaccine handover sheet, and the investigator will verify the name, batch number and quantity of the vaccine upon receiving.

***Vaccine registration and use records:*** the investigator shall establish vaccine registration and use records and distribute investigational vaccine and control vaccines according to the number of people in the observation groups.

***Vaccine recycle record:*** The abandoned, expired and remaining vaccines in this trial are returned to the Sponsor. Sponsor receives vaccines and verifies the batch number and quantity of vaccines, fills in the vaccine handover form, and makes relevant records, which are signed by the vaccine manager and Sponsor representatives.

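### The blinding provisions contradict each other: Section 9 unblinds after day 28 but Section 7.10 after month 12, and the labels and Section 6.3.3 conflict with number-only packaging and IWRS allocation

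*Protocol*

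**What the plan says.** **Timing.** Section 9 sets two triggers: "After obtaining the immunogenicity test results 14 days after the full course of immunization" and "completing the safety follow-up for 28 days". Then "the database is locked and unblinded to perform safety, immunogenicity and vaccine efficacy evaluation". The 12-month persistence bloods come later in the same sentence, before site closure. No limit is placed on who is unblinded.

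Section 7.10 opens with "All participants completed long-term safety observation for 12 months after vaccination and blood collection for 12 months after immunization". It then lists, as conditions for closing sites and starting the persistence evaluation, completion of all study requirements, database lock, blind data review, and unblinding of necessary study staff. The synopsis row on trial completion repeats these four conditions.

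Section 4.6.2 keeps the code sealed until database lock without saying which lock. Section 10.5 plans no interim analysis. Primary endpoint 5 (Section 4.3) is "The incidence of SAE and AESI observed after vaccination and up to 12 months after full course of immunization". Section 7.3.1 collects it through monthly telephone calls and participants' own reports.

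**Supplies.** Section 6.2 says the vaccines are "packaged in doses in boxes with the same appearance and only marked by the vaccine number". The illustrated box and vial labels that follow both carry the NVSI-06-09 name and a batch-number field, on the vial "Batch Number: XXXX". Section 6.3.3 has the investigator check name, batch number and quantity at handover, and then "distribute investigational vaccine and control vaccines according to the number of people in the observation groups". Section 4.6.1 instead has the investigator obtain a vaccine number from IWRS and vaccinate with it.

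**The concern.** The two timing rules cannot both be followed, and they differ by most of a year. SAE and AESI counts depend on what participants choose to report and on the investigator's judgement of causality (Section 4.5.3). COVID-19 case finding is mainly passive (Section 7.5), so blinded review by the endpoint committee cannot correct for which cases reach it. If allocation is known from about day 28, a difference between arms in these outcomes can no longer be separated from a difference in reporting.

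The supply text raises a separate risk that starts at vaccination. Someone who checks product name and batch at delivery, and later reads a batch number on each kit, may be able to link kits to arms. Such a leak would come before the diary period, so it would reach safety outcomes that the Section 9 timing does not.

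**Working it through.** The plan states no figure on this point, so there is nothing to reproduce. The check is one timing calculation and two comparisons of text.

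**1. Share of the SAE/AESI window after unblinding under Section 9**

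Inputs:
- 12 months = day 360 (Section 7.4, blood sample numbering rule)
- Safety trigger = day 28 (Section 9)
- Recruitment = 1 month; sample testing = about 1 month (Section 7.9)
- Day-28 visit window = +10 days (Schedule of Events)
- Assumption: 1 month = 30 days

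Formula: share = (360 − u) / 360, where u is the participant's own study day when the database is unblinded.

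| Case | u | Days left | Share | Share with +10 days |
|---|---|---|---|---|
| Unblinded at own day 28 (last enrolled, no delay) | 28 | 332 | 92% | 322/360 = 89% |
| First enrolled, after recruitment: 30 + 28 | 58 | 302 | 84% | 292/360 = 81% |
| First enrolled, plus testing: 30 + 28 + 30 | 88 | 272 | 76% | 262/360 = 73% |
| Unblinding after month 12 (Section 7.10) | 360 | 0 | 0% | 0% |

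The third row is the late end, because testing of day-14 samples can overlap the wait for 28-day safety. In months, 272/30 = 9.1 and 332/30 = 11.1.

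**2. Outcomes that fall after a Section 9 unblinding**

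| Outcome | Exposed by the timing? |
|---|---|
| Primary 1, day-14 titre and 4-fold rise | No; day-14 results are a trigger |
| Primary 2 and 3, 30 minutes and days 0–7 | No; complete |
| Primary 4, days 8–30 | At most the last 2 days (30 − 28) |
| Primary 5, SAE/AESI to month 12 | Yes, 76% to 92% of the window |
| Persistence at 3, 6, 9 and 12 months | Collected after it |
| Case surveillance (exploratory) | Mostly after it |

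**3. Supply provisions side by side**

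- Section 6.2 allows only a vaccine number on the box. The label illustration adds a product name and a batch number.
- Section 4.6.1 allocates by IWRS number. Section 6.3.3 has the investigator distribute the two vaccines by group size, which a blinded investigator cannot do.
- Section 6.3.3 also mentions a placebo, which this trial does not have.

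The possible route to the arm has three steps: name and batch are checked at handover (6.3.3); recipients log batch numbers (6.3.2); the box and vial labels are checked before injection (7.2.1). If the printed batch number is the true one, these steps join the arm to the kit. If it is masked or absent, they do not.

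Only one label design is shown. If it goes on both products, the name conceals the arm while misnaming the control. If the control carries its own name, the label reveals the arm directly.

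**The case against.** A reader might infer that the protocol undoes its own double blind. The documents do not support that. Section 7.10 and the synopsis give a later unblinding limited to necessary staff, and Section 7.5 requires blinded endpoint review. Section 9 unblinds the database; it does not say that sites or participants are told their allocation. What stands is that Section 9 gives a different date with no limit on access, and nothing says which section governs.

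A reader might also conclude that the timing compromises four of the five primary endpoints. It exposes endpoint 5 and at most two days of endpoint 4. Only the supply problem could reach endpoints 2 to 4.

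A third tempting inference is that the batch numbers reveal all 516 allocations because the vaccines come from different manufacturers. Section 6.1.1 lists one institute as a manufacturer of both. The label shows a blank or placeholder field, so nothing establishes that true batch numbers will be printed. Section 4.6.2 has labels applied under the randomization list by people outside the trial. The route is therefore conditional.

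Section 6.3.3 may be generic supply text, as the stray placebo suggests, and staged-lock mechanics often sit in an SAP or blinding plan not shown here. That is fair for the mechanics. It does not settle contradictory instructions to sites within the protocol.

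**Conclusion.** The point holds as two unreconciled contradictions, not as proof that the blind is broken.

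- **Timing.** Following Section 9 puts roughly 9 to 11 of 12 months of primary endpoint 5 after unblinding (76% to 92%; 73% at the lowest with a +10-day visit window). Following Section 7.10 puts none of it there. The range assumes 30-day months and the recruitment and testing times in Section 7.9. The bias arises only if people who report or judge events learn the allocation, which Section 9 neither states nor prevents.
- **Supplies.** The conflict of the labels with Section 6.2, and of Section 6.3.3 with IWRS allocation, is plain on the text. Whether site staff could identify the arm depends on true batch numbers being printed, or on the control carrying its own name. If either is so, primary endpoints 2 to 5 are open to knowledge of allocation.

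Day-28 titres are not among the Section 9 triggers. Adding them would be a preference, since the primary antibody endpoint is at day 14, and it forms no part of this point.

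**What to change.** - **Sections 9 and 7.10, and the synopsis row:** use one sequence throughout. State that any lock after day 28 unblinds only a named analysis group, and that participants, site staff, laboratory and endpoint committee stay blinded until the 12-month lock. Report endpoint 5 to day 28 at the first lock and in full at the final lock. In Section 4.6.2, say which lock opens the code, and for whom.
- **Section 6.2 and the label illustration:** use an identical label on both products, consistent with the number-only rule, with a masked batch number or none.
- **Section 6.3.3:** do site accountability by vaccine number, and delete distribution by group and the mention of placebo.

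The cost is protocol wording and label text. No added participants, visits or samples are needed, and Section 4.6.2 already provides an unblinded randomization statistician who could hold the batch list.
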